## 6.4. Criteria for Evaluation

### 6.4.1. Safety Evaluation

All subjects who receive study drug will be monitored for safety. Study drug adverse effects will be assessed continuously. Adverse events and other symptoms will be graded according to the National Cancer Institute Common Terminology Criteria for Adverse Events, Version 4.0 (Appendix 8: <http://ctep.cancer.gov>). All serious adverse events and adverse events regardless of study drug attribution will be recorded on the case report form and analyzed.

Each serious adverse event must be documented on the electronically available "**Serious adverse events report**" form. The completed form is automatically faxed (fax no. is filed automatically in the system) to the sponsor and Alcedis GmbH. In the event that electronic reporting is not possible, paper SAE forms in the investigator's file handed out at the beginning of the study are at the doctor's disposal for notification by conventional fax. An SAE report should be completed for any event where doubt exists regarding its status of seriousness. The collection of SAEs should begin following the subject's written consent to participate in the study. SAEs include any laboratory test result that meets the definition of an SAE. Adverse events leading to discontinuation from treatment must be documented on the electronically available "Adverse event report" form. These events also include any laboratory abnormality that required the subject to have ipilimumab discontinued.

### 6.4.2. Efficacy Evaluation

#### 6.4.2.1. *Definition of Measurable/Non-Measurable and Index/Non-Index Lesions*

Definitions of lesions are based on *RECIST criteria and immune-related response criteria (irRC)* in this study. For the evaluation of the therapeutic response in the study only the RECIST guidelines will be applied. The lesions evaluation by using irRC will be performed simultaneously.

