**Examinations:**

The disease will be assessed at baseline, at week 12 and for patients with stable disease or better responses, thereafter every 12 weeks in the absence of PD with a maximum of one year after receive of the first treatment. Response evaluation will be done according to immune-related response criteria (Wolchok et al., CCR 2009).

All patients who prematurely discontinued treatment due to a drug-related adverse event prior to Week 12 (in the absence of disease progression) will return for all study visits and procedures including Week 12 and, if appropriate, further re-staging assessments. Any patient with documented progression at any scheduled re-staging visit and who will not receive any re-induction will undergo no further re-staging visits.

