#### **1.3.7 Rationale for using immune-related Tumor Assessment Criteria (irRC)**

Ipilimumab is an immuno-stimulating antibody with evidence of anti-cancer activity (durable objective response and stable disease) in subjects with advanced melanoma, including subjects with established brain disease. Observations of clinical activity defined by tumor response endpoints defined by conventional criteria (eg, mWHO) may be inadequate to realize the kinetics and magnitude of clinical benefit achieved with ipilimumab.

Histopathological evidence has demonstrated ipilimumab can produce an influx or expansion of tumor infiltrating lymphocytes (Townsend et al., 1993). Therefore, early increases in lesion size detected radiologically or upon gross examination could be misinterpreted as progressive tumor growth and precede objective tumor shrinkage. In addition the appearance of new lesions may have categorized a subject to have progressive disease using conventional tumor assessment criteria despite the concurrent observation of objective tumor responses in preexisting lesions and a net reduction in global tumor burden that includes the new lesions.

Hence the appearance of new lesions in and of themselves may not necessarily constitute progressive disease. The immune-related response criteria (irRC) were developed as a tool to gauge tumor response using the changes in global tumor burden (Wolchok et al., 2009). In addition, the irRC may be useful to inform a physician's decision to continue dosing in subjects who may receive benefit from additional ipilimumab therapy. The ir-response assessment is

based solely on objective measurements (SPD) of index and new lesions. Non-index lesions are not considered. The irRC identified 9.7% of subjects (22/227 treated subjects) from CA184022 and CA184008 at 10 mg/kg who demonstrated disease control in the form of stable or reduced measurable tumor burden, including new lesions, at or after disease progression by mWHO.

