## 5 STUDY THERAPY WITH IPILIMUMAB

### 5.1 Induction Treatment

Subjects enrolled after IC will receive ipilimumab according to the protocol of the completed Medarex study MDX010-20 (Hodi et al., NEJM, 2010) as a single agent at a dose of 3mg/kg for 4 times over 10 weeks (1 cycle): The day subjects receive the first dose of protocol ipilimumab therapy will define Day 1. Ipilimumab, 3 mg/kg, day 1 (W1), 22 (W4), 43 (W7), 64 (W10) must be administered intravenously over a 90-minute period every 3 weeks for a total of four doses, as tolerated. This dose demonstrated an overall survival benefit for the first time in treating metastatic melanoma in a controlled randomized clinical study (Hodi et al., NEJM, 2010).

- Electrocardiogram (ECG) examination should be performed during screening and week 12. Patients with an existing myocarditis are excluded from this study. For patients with suspicion of myocarditis e.g. dyspnoea, functional insufficiency etc. ECG examinations have to be performed before each treatment.
- Laboratory evaluations should be performed (refer to section 6.1.1.2) and the results examined before administration of each ipilimumab dose.
- As durable disease stabilization and/or objective tumor response can be seen after early progression before Week 12, it is recommended that, in the absence of dose-limiting toxicities (eg, serious irAEs), all four doses of ipilimumab be administered over the initial 12 weeks even in the setting of apparent clinical progression, providing the subject's performance status remains stable.
- All subjects who enter the induction period, including those who may have discontinued treatment for drug-related AEs should obtain a 12-week, 24-week 36-week and 48 week tumor assessment. Those patients who have evidence of clinical progression during the induction period, should obtain further tumor assessment according to Standard of Care.
- Based on clinical experience in the ongoing and completed melanoma studies, the following recommendations apply for subject management in light of the Week 12 or later tumor assessments:
  - The appearance of new lesions in subjects with other stable or shrinking baseline tumor burden may be experiencing clinical benefit and should continue in follow-up before alternative anti-cancer agents are considered. These subjects can be seen to have continued tumor shrinkage in follow-up scans.

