## **6. STUDY PROCEDURES AND OBSERVATIONS**

### **6.1. Procedures by Visit**

#### **6.1.1. Study Procedures by Visit and Treatment Cycle**

Note that results of all safety laboratory tests (that is, all chemistry and all hematology results) must be obtained and reviewed before ipilimumab administration, as applicable. All laboratory results must be within the established range before ipilimumab is administered. All induction period laboratory samples must be collected within a window of up to 3 days before administration of ipilimumab. Laboratory evaluations using a local laboratory must be performed and the result examined by the investigator before administration of each dose of ipilimumab.

The disease will be assessed at baseline, after 12 weeks and for patients with stable disease or better responses, thereafter every 12 weeks in the absence of PD to a maximum of one year. Response evaluation will be done according to RECIST and immune-related response criteria (1).

All patients who prematurely discontinue treatment due to a drug-related adverse event prior to Week 12 (in the absence of disease progression) will return for all study visits and procedures including Week 12 and, if appropriate, further re-staging assessments until disease progression is observed.

- Subjects who are no longer receiving ipilimumab because of unacceptable toxicity (refractory Grade  $\geq 3$  irAEs) or due to investigator judgment are followed with tumour assessment until ir PD. Efficacy assessments for these subjects during follow-up are as per the standard of care. Date of death is recorded.
- Subjects who discontinue ipilimumab treatments are followed with tumour assessment until ir PD and should be followed until death or the closure of the study (whichever is first).
- Subjects who are no longer receiving ipilimumab because of progression and who have switched to alternative treatment are not followed formally except to record the date of death.

Any patient with documented progression at any scheduled re-staging visit who is not eligible for re-induction treatment will undergo no further re-staging visits and enters the Follow up phase (FU phase).

At the time of closure of the study (LPFV+12 months), it will be ensured that survival status (alive/dead and date) has been collected for each subject for each subject's full follow-up period (i.e: for 1 year from the subject's first treatment dose).

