#### 9.5. Statistical analysis

The primary endpoint, one year survival rate, is based on the ITT population. As a simple rate, it will be calculated as the number of patients being still alive 12 months after their first administration of the study treatment divided by the number of patients having received at least one administration of the study treatment. Only subjects known to be alive at 1 year will be included in the numerator. As a time to event variable, it will be derived from the Kaplan-Meier curve. In this case missing data will be censored at the last contact. See below for further details.

All other analyses will have exploratory character. Results will be presented overall and per cohort/subgroup:

- (1) cutaneous vs uveal vs. mucosal melanoma
- (2) - LDH < 2 UNL versus LDH ≥ 2 UNL
- (3) - status brain mets versus no brain mets in medical history
- (4) - status Braf mutation positive versus. Braf mutation negative
- (5) - HLA-A2 positive versus HLA-A2 negative

Demographic and baseline characteristics will be tabulated for all treated subjects. For categorical variables, summary tabulations of the number and percentage within each category (with a category for missing data) of the parameter will be presented. For continuous variables, the mean, median, standard deviation, minimum and maximum values will be given.

Proportions (Survival rate at 1 year, irOR, irDCR, irPFS at 6 mths, OR and DCR) will be presented with exact (Clopper and Pearson) two-sided 95% CI. irOR, irDCR and irPFS are defined according to the irRC; OR and DCR according to RECIST; The date of origin for the survival rate at one year, and irPFS at 6 months is the date of the first ipilimumab dose. Only subjects known to be progression free at 6 months / alive at 1 year will be included in the respective numerators. Any subject receiving at least one dose of ipilimumab will be included in the denominators. The denominator for the irOS and irPFS analyses will be the ITT population. The denominator for the irOR, and irDCR, OR and DCR will be the Response-evaluable population..

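### Section 6.4.2.1 applies RECIST alone to response, the progression that ends re-staging is not tied to a criterion, and the 6-month PFS numerator has no scan at 6 months; secondary endpoints only

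*Protocol*

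**What the plan says.** On the response criterion, Protocol section 6.4.2.1 says "For the evaluation of the therapeutic response in the study only the RECIST guidelines will be applied", followed at once by "The lesions evaluation by using irRC will be performed simultaneously". The Synopsis (Examinations) says "Response evaluation will be done according to immune-related response criteria" and names no other criterion. Section 6.1.1 says "Response evaluation will be done according to RECIST and immune-related response criteria", and section 6.4.5 also names both. Sections 9.3.2 and 9.5 define irOR, irDCR and PFS by irRC, and OR and DCR by RECIST.

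On the end of scanning, section 6.1.1 provides that a patient with documented progression who is not eligible for re-induction "will undergo no further re-staging visits and enters the Follow up phase (FU phase". The Synopsis has a similar rule, and section 6.1.1.3 runs 12-weekly imaging until progression. None of the three says which progression is meant. Elsewhere, section 6.1.1 follows subjects who are off ipilimumab until irPD. Section 5.1 says that all who enter induction "should obtain a 12-week, 24-week 36-week and 48 week tumor assessment", and moves patients with clinical progression during induction to standard-of-care assessment.

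On the PFS rate, section 9.5 says "Only subjects known to be progression free at 6 months / alive at 1 year will be included in the respective numerators", with every treated patient in the denominator. For Kaplan-Meier, the same section censors patients not known to have progressed or died at their last tumour assessment.

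**The concern.** Two separate things are at stake.

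The first is whether the scans behind the irRC endpoints will be taken. Section 6.4.2.1 points a site to RECIST, and the stopping rule for re-staging leaves the criterion open. Sites may therefore stop at different events. A scan that was never taken cannot be restored by any later analysis rule. Section 6.4.5 itself describes this loss: conventional PD ends imaging and hides a later immune-mediated response.

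The second is how the 6-month PFS rate is counted. It is to be reported as a simple proportion and from Kaplan-Meier. The two treat the same patient differently when the last clear scan precedes the landmark, and the regular schedule places a scan just before it.

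**Working it through.** **1. Which criterion governs**

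| Protocol place | Criterion |
|---|---|
| Synopsis, Examinations | irRC |
| 6.1.1 and 6.4.5 | RECIST and irRC |
| 6.4.2.1 | RECIST only, with irRC lesion evaluation in parallel |
| 9.3.2 and 9.5 | irRC for irOR, irDCR and PFS; RECIST for OR and DCR |

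The first sentence of 6.4.2.1 is out of line with the rest. The second shows that irRC measurements are planned, but does not say which criterion governs a decision such as ending re-staging.

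**2. What ends scanning**

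| Protocol place | Rule | Criterion named |
|---|---|---|
| Synopsis; 6.1.1 | stop at documented progression if no re-induction | none |
| 6.1.1.3 | every 12 weeks until progression | none |
| 6.1.1, subjects off ipilimumab | continue until irPD | irPD |
| 5.1 | weeks 12, 24, 36 and 48 for all who enter induction; standard of care after clinical progression in induction | none |

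**3. Why the missing name matters.** Take a patient whose index lesions shrink by week 12 and who has one small new lesion.
- Under RECIST (6.4.3.1) this is PD.
- Under irRC (6.4.4.3) the new lesion only adds to the tumour burden. The patient is not irPD unless the total rises by 25%.
- If the site stops at RECIST PD, the week-12 scan still allows irSD to be recorded. An irPR or irCR that needs a later or confirming scan (6.4.4.5) is lost, and irRC-based PFS is censored at week 12 unless the patient dies.
- If the site stops at irPD, scanning continues.

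**4. Size of that loss.** The only related figure is in section 1.3.7: "The irRC identified 9.7% of subjects (22/227 treated subjects". It reproduces: 22/227 = 0.097. It is at most an upper bound here. It counts disease control at or after progression, and control visible at the progression scan would not be lost. It is relative to mWHO rather than RECIST. It comes from studies at 10 mg/kg with maintenance dosing (section 1.3.6). It would also require every site to stop at RECIST PD.

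**5. The PFS landmark**
- 6 months = 6 × 365.25/12 = 182.6 days.
- Week 24 = 24 × 7 = day 168, which is 14.6 days before the landmark (5.52 months).
- Week 36 = 36 × 7 = day 252, which is 69.4 days after it (8.28 months).
- If week 10 is day 64, as in section 5.1, week 24 opens on day 1 + 7 × 23 = 162 and week 36 on day 1 + 7 × 35 = 246. The landmark still lies between them.
- No window is given for re-staging scans. An assumed 7 days' lateness takes week 24 to day 175, still 7.6 days short.

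**6. Effect on the two PFS rates.** Take a patient clear at day 168, with no later scan and no death. In the simple rate (9.5) the patient is not known to be progression free at day 182.6, so is in the denominator only. In Kaplan-Meier the patient is censored at day 168. With N = 200 treated, k such patients lower the simple rate by k/200: 5 patients make 2.5 points, 10 make 5 points, 20 make 10 points. The documents give no basis for k; these values are assumptions.

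**7. What a week-24 numerator would cost in accuracy.** Assume exponential PFS, S(t) = 2^(−t/median), with medians that are assumptions because the documents give none:

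| Median (months) | S at 5.52 months | S at 6 months | Excess (points) |
|---|---|---|---|
| 2 | 14.8% | 12.5% | 2.3 |
| 3 | 27.9% | 25.0% | 2.9 |
| 4 | 38.4% | 35.4% | 3.1 |
| 6 | 52.9% | 50.0% | 2.9 |

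Using the week-24 scan overstates a true 6-month rate by about 2 to 3 points.

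**The case against.** The best defence is that irRC is well provided for. Section 6.4.2.1 itself plans irRC evaluation in parallel. Section 6.4.4 defines it fully, and section 9 already assigns irRC to irOR, irDCR and PFS. Several passages lean towards irPD as the end of scanning: irRC is the only criterion named in the Synopsis rule, 6.1.1 follows subjects off drug until irPD, and 5.1 keeps patients with new lesions but a stable or shrinking baseline burden in follow-up. Scans 12 weeks apart also satisfy the requirement to confirm a response no less than 4 weeks later. All of this stands. A reader might infer from the contradictions that the irRC endpoints cannot be observed as defined; the documents do not support that. The loss arises only where a site actually stops at RECIST PD.

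The defence does not remove the RECIST-only sentence or supply the missing criterion. The irPD bullets cover subjects off ipilimumab, and the first of them leaves efficacy assessment to standard of care.

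On the landmark, assessment windows are often left to an SAP, and a Kaplan-Meier 6-month rate is planned as well. That is fair. But the numerator rule is fixed in section 9.5, so the conflict with censoring is already in the Protocol.

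**Conclusion.** The point holds as an inconsistency with a cheap correction. It affects secondary endpoints only: irOR, irDCR and the 6-month PFS rate. The primary 1-year survival rate is untouched, because survival is followed whether or not scanning continues.

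The extent of lost irRC information is unknown. A reader might multiply 9.7% by 200 and infer about 19 patients with unobservable benefit. For the reasons in step 4, that product is not an expected count.

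A reader might also infer that the plan reports an 8-month rate as a 6-month rate. It does not. PFS runs to the first documented irPD or death, so a patient clear at week 24 with irPD first seen at week 36 has PFS beyond 6 months and is progression free at the landmark. What remains is the patient with no scan after week 24: 0.5 points each at N = 200, in an unknown number. The two problems can also combine. A patient whose scans stop at week 24 for RECIST PD without irPD falls into exactly this group.

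**What to change.** - In section 6.4.2.1, replace the RECIST-only sentence. State that irRC governs PFS, irOR and irDCR, and that RECIST governs OR and DCR in parallel.
- In the Synopsis (Examinations) and sections 6.1.1 and 6.1.1.3, name irPD as the event that ends protocol re-staging, and reconcile these passages with section 5.1. Because irPD then carries this rule, also reconcile its reference value: section 6.4.4.1 uses the nadir and section 6.4.4.4 the baseline.
- In section 9.5 and the matching Synopsis text, define the 6-month PFS numerator as alive with no documented irPD through the week-24 assessment, with a stated window. Say how a death between that scan and day 182.6 counts.

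The cost is Protocol wording. Some patients with RECIST PD but no irPD would keep scans that section 5.1 mostly schedules already. Under the assumptions in step 7, the week-24 numerator is about 2 to 3 points more favourable than a true 6-month rate, and the report should say so.

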#### 6.4.2.2. *Definition of Measurable and Non-Measurable Lesions*

- Measurable lesions are lesions that can be accurately measured in at least one dimension with longest diameter at least 20 mm using conventional X-ray, CT or MRI techniques, or at least 10 mm with spiral CT scan. Skin lesions can be considered measurable.
- **Non-Measurable (evaluable) Lesions** are all other lesions, including unidimensionally measurable disease and small lesions (lesions without at least one diameter  $\geq 20$  mm), and any of the following:
  - Lesions occurring in a previously irradiated area (unless they are documented as new lesions since the completion of radiation therapy), bone lesions, leptomeningeal disease, ascites, pleural or pericardial effusion, lymphangitis cutis/pulmonis, abdominal

masses that are not pathologically/cytologically confirmed and followed by imaging techniques and cystic lesions.

- All measurable and non-measurable lesions should be measured at screening and at the defined tumor assessment timepoints (every 12 weeks).

#### **6.4.2.3. Definition of Index/Non-Index Lesions**

All measurable lesions, up to a maximum of **two lesions per organ** and **five lesions in total**, should be identified as *index* lesions to be measured and recorded on the medical record at Screening. The *index* lesions should be representative of all involved organs. In addition, *index* lesions should be selected based on their size (lesions with the longest diameters), their suitability for accurate repeat assessment by imaging techniques, and how representative they are of the patient's tumor burden. At Screening, a sum of the products of diameters (SPD) for all *index* lesions will be calculated and considered the baseline sum of the products of diameters. Response criteria to be followed are listed below. The baseline sum will be used as the reference point to determine the objective tumor response of the *index* lesions at tumor assessment (TA).

Measurable lesions, other than *index* lesions, and all sites of non-measurable disease, will be identified as *non-index* lesions. *Non-index* lesions will be recorded on the medical record and should be evaluated at the same assessment time points as the *index* lesions. In subsequent assessments, *non-index* lesions will be recorded as "stable or decreased disease," "absent," or "progression."

#### **6.4.3. Evaluation of Tumor Response Using RECIST Criteria**

##### **6.4.3.1. Definition of Measurable Lesion Response Using RECIST Criteria**

Measurable lesion will be measured in a dimension using the longest diameter is used. The tumour response will be investigated during every re-staging visit.

Complete response (CR): Disappearance of all lesions and appearance of no new lesions.

Partial response (PR): At least a 30% decrease in the sum of the longest diameter of measurable lesions. No new lesions may occur or individual lesions progress.

Progressive disease (PD): At least a 20% increase in the total of the longest diameters of measurable lesions (as reference to the smallest sum recorded since the treatment started) or the appearance of new lesions.

If the measurable lesion disappears and the progression of a lesion or the appearance of new lesions is observed elsewhere at the same time, this is also documented as a progressive disease.

Stable disease (SD): Neither a partial nor a complete response in the absence of progression.

